## Interventions

### Explanation for the choice of comparators {6b}

#### Conventional treatment regimen

All patients will receive standard treatment according to recently published guidelines [7, 8], including fluid therapy, nutritional supplementation, routine medical treatment such as proton pump inhibitors, analgesia and antibiotics as indicated, organ supportive therapy, and ERCP if necessary. Nasogastric and annal tubes will be used for patients with intra-abdominal hypertension (IAH) or abdominal compartment syndrome (ACS). For patients with persistent ACS or new-onset organ failure, percutaneous drainage of ascites and surgical abdominal decompression will be considered [37, 38]. When pancreatic infection occurs, either a surgical or endoscopic step-up approach considering the location of the necrotic collection and the technical availability will be applied.

#### Study herbal formulation

The prescription of CQCQD was developed by this research team and standardised to contain 13 Chinese medicines, the contents of which can be found in Table 1.

**Table 1 Tab1:** The ingredients list of standardised Chinese herbal medicine prescription of CQCQD

Ingredients	Latin name	Plant name	Weight (g)
Dahuang	*Rhei Radix et Rhizoma*	*Rheum palmatum* L.	15
Houpo	*Magnoliae Officinalis Cortex*	*Magnolia officinalis* Rehd. et Wils.	15
Zhizi	*Gardeniae Fructus*	*Gardenia jasminoides* Ellis	15
Zhuyechaihu	*Bupleuri Radix*	*Bupleurum chinese* DC.	15
Huangqin	*Scutellariae Radix*	*Scutellaria baicalensis* Georgi	15
Chuanxiong	*Chuanxiong Rhizoma*	*Ligusticum chuanxiong Hort.*	15
Honghua	*Carthami Flos*	*Carthamus tinctorius* L.	10
Zhishi	*Aurantii Fructus Immaturus*	*Citrus aurantium* L.	15
Yanhusuo	*Corydalis Rhizoma*	*Corydalis yanhusuo* W. T. Wang	15
Muxiang	*Auklandiae Radix*	*Aucklandia lappa* Decne.	15
Chishao	*Paeonia Radix Rubra*	*Paeonia veitchii* Lynch	15
Gancao	*Glycyrrhizae Radix et Rhizoma*	*Glycyrrhiza uralensis Fisch.*	3
Mangxiao	*Natrii Sulfas*	Na_2_SO_4_ • 10H_2_O	30

Due to the absence of a positive control drug for AP and the difficulty in preparing a placebo for the decoction, we will utilise a low-dose arm administering 10% CQCQD of similar colour and odour by adding dextrin and colourant, which intend to mimic the placebo group as a control [39]. Generally, the selection of control in a pragmatic trial is usually based on conventional or standard treatment, and placebo is not routinely used as a control. However, the placebo is applied in our trial for following the reasons: (1) The standard treatment for AP including analgesia and fluid therapy is needed in all AP patients and cannot be used only in the control group. (2) Placebo control is designed in our trial to minimise the expectant effect of participants and researchers, as well as to control bias caused by psychological factors from researchers, participants, and evaluators.

The raw herbal drugs with quality certificates will be supplied by Chengdu Kangmei Pharmaceutical Company Limited, Co., Ltd., China. Quality-controlled CQCQD and placebo decoctions will be prepared by the Department of Pharmaceutical Preparation of West China Hospital using the Good Manufacturing Practice standards, according to the 2005 Edition of the Chinese Pharmacopoeia. The high-performance liquid chromatography–mass spectrometry method is used for the quality control of CQCQD. The preparation of the CQCQD and placebo is prepared by two independent pharmacists. During the procedure, a double check will be made by the pharmacist and the researcher. Finally, CQCQD and placebo decoctions will be labelled with computerised numbers to prevent the intervention and control from mixing up. The study decoction preparations will be transported to the inpatient ward and dispensed by two individual research assistants. Researchers will provide the study decoction solution for free. Study investigators and subjects do not know which decoction preparation will be used.

### Intervention description {11a}

#### Administration of randomised drugs guided by the AGI-based algorithm

The AGI grade has been widely used to assess gastrointestinal injury in patients with acute critical illness [11, 40]. Evidence has shown that the AGI grading system is useful for identifying the severity of gastrointestinal dysfunction/failure in AP [41]. In our study, the participants will receive randomised drugs guided by the AGI-based algorithm (Fig. 1).Initiation: If the Bedside Index of Severity in Acute Pancreatitis (BISAP) score or Glasgow Criteria System (GCS) < 2 at allocation [42, 43], the patients will empirically receive CQCQD or placebo 200 mL oral intake (or intragastric infusion) and enema, 3 times a day. If the patients have a BISAP/GCS score ≥ 2 at allocation, they will be required to receive urethral catheterisation to monitor intra-abdominal pressure (IAP) every 4 h, which is the key index in AGI grade. The dosage and frequency of decoction is determined by AGI grading according to the following criteria: (1) if AGI grade = 1, 200 mL CQCQD or placebo is administered orally (or intragastrical infusion) and enema, 3 times a day; (2) if AGI grade = 2, CQCQD or placebo is given 100 mL orally (or intragastrical infusion) and 200 mL enema, every 6 h; (3) if AGI grade = 3, CQCQD or placebo are given 100 mL orally (or intragastric infusion) and 200 mL enema, every 4 h; (4) if AGI grade = 4, CQCQD or placebo is given 100 mL orally (or intragastric infusion) and 200 mL enema, every 2 h. If the patient with a BISAP/GCS score ≥ 2 at allocation rejects urethral catheterisation, the initial administration of the randomised drug is in accordance with AGI grade 1, and the conditions will be reassessed for further judgement.Continuation: AGI grade is evaluated daily at 7–8 am by the researchers. The dosage and frequency of CQCQD or placebo are determined by the corresponding AGI grade at the time points.Termination: CQCQD or placebo is administered for at least 5 days and no more than 14 days. IAP monitoring will be terminated if it is less than 15 mmHg for two consecutive days. CQCQD or placebo will be terminated, if AGI grade < 1 for two consecutive days, or normally oral refeeding without discomfort. Other conditions will be determined by clinical treatment leaders and principal investigators.The upgrade principle for patients with AGI grade 1 initially or who reject urethral catheterisation: (1) the aggravation of abdominal distension and constipation; (2) the occurrence of new organ dysfunction; (3) the deterioration of the original organ function; and (4) other conditions will be assessed and determined by clinical treatment leaders and principal investigators.

### Criteria for discontinuing or modifying allocated interventions {11b}

The patients are withdrawal if they meet any of the following criteria:Having manifestations of gastrointestinal perforation, bleeding, mechanical ileus, severe haemorrhoids, and anal fissure which require restricted fast and enema.Quitting voluntarily.Adverse medical events occurring during the study, such as severe hypernatremia, intolerance to critically worsening conditions, or other reasons as judged by the investigators, which might make the patient unlikely to complete the study.

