## Data collect and management

### Plans for assessment and collection of outcomes {18a}

According to the study schedule shown in Table 2, data will be collected during the index admission and 26 weeks after enrolment. If a participant wishes to discontinue the study drug or the treating physician believes a participant should discontinue the study drug due to medical conditions, the investigator will communicate with the participant and the treating physician to obtain the reasons and record in CRF. Further follow-up will still be performed unless the participant withdraws from the trial.

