### Methods in analysis to handle protocol non-adherence and any statistical methods to handle missing data {20c}

The data will be analysed based on the full analysis set (FAS), per-protocol set, and safety set. FAS analysis is the basic principle of intention-to-treat, including all the enrolled patients in the trial. Analysis will follow intention-to-treat principles with patients analysed according to randomisation and irrespective of actual use or compliance with the algorithm. The per-protocol analysis is the subset of FAS analysis, which just includes patients who finish the trial completely. The safety set analysis is the set of patients who receive the treatment and have safety assessment. Missing values will be addressed by multiple imputation, having appropriately explored the missingness mechanism and in accordance with good practice.

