### Adverse event reporting and harms {22}

Adverse events (AEs) are defined in accordance with the National Cancer Institute-Common Terminology Criteria for Adverse Events. The common aberrations in symptoms, signs, and laboratory values due to the severity of the underlying disease and the impact of standard therapies will not necessarily constitute an AE unless they require significant intervention or are of concern in the investigator’s clinical judgement. If severe adverse events (SAEs) happen that threaten the patients’ safety, the researcher should stop the study at once, cancel the blinding, and take any measures to rescue the patients’ lives who experience SAE.

All details of any AE/SAE will be documented and reported during the treatment and the follow-ups. Furthermore, SAE will be reported to the principal investigator and the BREC immediately to decide whether the patient should withdraw from the trial.

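### The protocol does not separate stopping the decoction from leaving the trial, so day-28 data can be lost for outcome-related reasons, and its per-protocol set measures completion, not adherence

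*Protocol article*

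**What the plan says.** Four sections of the protocol article bear on this.

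- **{11b}, discontinuing or modifying the intervention.** The heading concerns the intervention, but the text concerns the patient: "The patients are withdrawal if they meet any of the following criteria". The first criterion is "Having manifestations of gastrointestinal perforation, bleeding, mechanical ileus, severe haemorrhoids, and anal fissure which require restricted fast and enema". Another covers adverse medical events, "such as severe hypernatremia, intolerance to critically worsening conditions, or other reasons as judged by the investigators", and closes with "which might make the patient unlikely to complete the study". Voluntary quitting is the third ground.
- **{18a}, collection of outcomes.** When the participant wants to stop the study drug, or the treating physician thinks it should stop for medical reasons, the reasons are recorded. Then: "Further follow-up will still be performed unless the participant withdraws from the trial".
- **{22}, harms.** SAEs go to the principal investigator and the ethics committee "to decide whether the patient should withdraw from the trial".
- **{20c}, non-adherence and missing data.** "FAS analysis is the basic principle of intention-to-treat, including all the enrolled patients in the trial". Patients are analysed as randomised whatever treatment they actually took, and missing values are multiply imputed after the missingness mechanism has been explored. The per-protocol set is the subset "which just includes patients who finish the trial completely".

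**The concern.** The primary outcome is the duration of respiratory failure over 28 days. The criteria in {11b} are met after randomisation, are tied to how ill the patient is, and are partly discretionary. If meeting one ends observation, the days lost are likely to come from patients with long respiratory failure. Their outcome is then missing for a reason related to the outcome itself, which standard multiple imputation handles only as far as the observed data explain it.

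Imbalance between arms is plausible from the protocol's own facts. The active prescription contains 30 g of sodium sulfate and 15 g of rhubarb, control is a 10% strength decoction, and severe hypernatraemia is a named criterion.

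The per-protocol definition is a second, separate weakness. Finishing the trial does not show that treatment was received as planned. Agreement between such a set and the full analysis set would therefore say nothing about adherence.

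**Working it through.** **Step 1: trace one event through the text.** Suppose a patient has an adverse event that meets {11b}.

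- If the site treats it as the physician stopping the study drug, {18a} applies and follow-up continues.
- If the site treats it as {11b} words it (the patient is withdrawn), or as a decision under {22} to leave the trial, the exception in {18a} applies and follow-up can end.

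The same event leads to two different amounts of outcome data, and the text does not say which route applies.

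**Step 2: follow the patient into the analysis sets.**

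- Full analysis set: included on either route. On the second route the remaining days to day 28 are imputed unless they are collected anyway.
- Per-protocol set: excluded on the second route, even if treated exactly as the algorithm required until then. A patient who did not follow the algorithm but finished the trial is included.
- Deaths: {20c} does not say whether a patient who dies has finished. The natural reading may exclude them.

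**Step 3: scale of loss that the plan allows for.** The sample size section inflates 111 per group for 10% dropout: 111 / (1 − 0.10) = 123.3, rounded up to 124, and 2 × 124 = 248. This step reproduces. Expected loss is 124 × 0.10 = 12.4, about 12 patients per arm. It is general dropout and is not broken down by reason or arm.

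**Step 4: what selection does to a completers-only comparison.** Let w be the share withdrawn in an arm and D the mean duration in withdrawn patients minus that in retained patients. The mean over all patients is the retained mean plus w × D. With the same D in both arms, the error in the retained-patient difference (active minus control) is −(w_active − w_control) × D.

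The documents give neither w nor D, so every value below is an assumption.

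| Withdrawn, active / control | D (days) | Error (days) | Share of 2-day target |
|---|---|---|---|
| 10% / 10% | any | 0 | 0% |
| 15% / 5% | 2 | −0.2 | 10% |
| 15% / 5% | 4.5 | −0.45 | 22.5% |
| 15% / 5% | 9 | −0.9 | 45% |
| 10% / 5% | 10 | −0.5 | 25% |

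The last row written out, with 14 days in withdrawn and 4 in retained patients:

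- active: 0.90 × 4 + 0.10 × 14 = 5.0
- control: 0.95 × 4 + 0.05 × 14 = 4.5
- all patients: 5.0 − 4.5 = 0.5 days longer on active
- completers: 4.0 − 4.0 = 0

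A negative error flatters the active arm. If more patients were withdrawn from control, the sign would reverse.

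**The case against.** A reader might infer that the analysed patients as a whole are selected on outcome, so that the intention-to-treat claim is false. The documents do not support that. {20c} keeps all enrolled patients in the full analysis set as randomised, and no section removes an {11b} patient from it. A restricted per-protocol set beside a full analysis set does not contradict intention-to-treat.

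{18a} already continues follow-up when the physician stops the study drug for medical reasons. Read with its heading and with {18a}, the ungrammatical sentence in {11b} could mean withdrawal from the decoction only, and the exception in {18a} is worded as the participant's own act. This is a fair reading, but it does not settle the matter. {11b} itself speaks of completing the study, and {22} describes withdrawal from the trial as something that others decide.

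The size is also open to challenge. The rates are assumed, and the 10-day gap in the 0.5-day example is more than twice the planned SD of 4.5 days. The arithmetic describes completers only. It does not carry over to the full analysis set, where later days may be recoverable from hospital records and imputation may explain part of the loss. All of this stands.

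Finally, detailed per-protocol rules and the imputation model normally sit in an analysis plan, which is not at hand. That excuses missing detail. It does not excuse the definition the protocol does state, which rests on completion alone. That every death is excluded remains an inference.

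**Conclusion.** The point holds in a limited form.

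1. {11b}, {18a}, {20c} and {22} do not separate discontinuing the decoction from leaving the trial. Read literally, patients withdrawn under {11b} or {22} can lose their remaining day-28 respiratory SOFA data for outcome-related reasons. They stay in the full analysis set, but their contribution would rest on imputation. That set is affected only as far as outcomes after withdrawal go uncollected and imputation does not capture why they are missing.
2. The per-protocol set is selected on post-randomisation events, possibly including death, and cannot serve as a check on adherence.

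The size of any bias is unknown, because the documents give no withdrawal rates by arm or reason. For a completers-only comparison it is zero when withdrawal and severity are equal across arms, and 0.2 to 0.9 days in the assumed 15% against 5% scenarios. The 0.5-day example should not be read as an estimate of bias in the full-set result. The correction is worth making, but the point does not show that the primary analysis is invalid.

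**What to change.** - Reconcile {11b}, {18a}, {20c} and {22}. Record the meeting of a listed criterion, or an SAE decision, as discontinuation of the study decoction, with respiratory SOFA collected to day 28 and the other outcomes to week 26. Only withdrawal of consent ends outcome collection. The clinical criteria themselves stay as they are, and no view is taken on them.
- State in {20c} that the full analysis set is the primary set and the per-protocol set is supportive.
- Define the per-protocol set by eligibility and by treatment received according to the algorithm while on treatment, not by completion of the trial, and say that deaths are retained.

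The cost is a change of wording, plus slightly more data collection for the few patients who stop the decoction. Collection during the index admission and to week 26 is already planned, and most inpatient data should be in the hospital record.

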### Strategies to improve adherence to interventions {11c}

Although flex of experimental intervention adherence is used (Additional file 2), efforts will be made to improve adherence to intervention: patient education (educate patients about the necessity of urethral catheterisation to monitor IAP, educate their individual risk of disease-related complications) and medication-taking reminders (researchers monitor and reminder the frequencies and volume of medication).

### Relevant concomitant care permitted or prohibited during the trial {11d}

During hospitalisation, the patients are not allowed to use other Chinese medicines and alternative therapies (e.g. herbal extract injection, acupuncture, abdominal ultrasound therapy). Drugs for inhibitory gastrointestinal motility (e.g. catecholamines, sedatives) and prokinetics (e.g. neostigmine, domperidone, metoclopramide, erythromycin) are not used routinely unless the patients present with AGI grade 4 or other critical conditions suggested by clinical treatment leaders and principal investigators to ensure the safety of the patients. All the additional drugs or therapies must be recorded in case report form (CRF) in detail.

### Provisions for post-trial care {30}

Participants who are discharged and re-admitted within 4 weeks will be regarded as a re-admission for the same episode of care and will be in the same arm as their original allocation. Data of re-admission elsewhere will be collected at follow-up typically at 4 weeks.

### Outcomes {12}

#### Primary outcome measurements

Referring to the existing study results and expert recommendations [6, 28, 29, 44], the duration of respiratory failure (SOFA score ≥ 2 points for respiratory) within 28 days after admission will be served as the primary outcome in the CAP trial.

#### Secondary outcome measurements

I.Secondary outcomes during the index admissionThe occurrence of new-onset of any organ failure (SOFA score for respiratory, cardiovascular, or renal system ≥ 2 points) or new-onset of POF (organ failure lasts > 48 h). New onset is defined as events that occur after randomisation and not present 24 h before randomisation.Cumulative levels of C-reactive protein (CRP) on days 1, 2, 3, 5, 7, 14, 21, and 28 after admission.Levels of albumin, procalcitonin, interleukin-6 (IL-6), and neutrophil count on day 0, day 3, day 5, day 7, and day 14.Daily visual analogue scale (VAS) score of pain [45].Daily Pancreatitis Activity Scoring System (PASS) score within the 1st week after enrolment [46].Duration (days) of Systemic Inflammatory Response Syndrome (SIRS ≥ 2 points) [47].Duration (days) of fasting.The requirement of the anal tube.The requirement of prokinetic agents.Duration (days) of gastrointestinal decompression.Duration (days) of IAH and ACS.The receipt of respiratory support and renal replacement therapy.Length of intensive care unit (ICU) stays.Local pancreatic injury by contrast-enhanced computerised tomography (CECT) on days 7 and 14.Potential safety signals.Length of hospital stay.In-hospital cost.II.Secondary outcomes within 26 weeks after enrolmentThe requirement for catheter drainage or necrosectomy.Infected pancreatic necrosis.All-cause mortality.Self-report health situation by five-level EuroQol five-dimensional (EQ-5D-5L) [48].

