**Methods:**

This is a single-centre, randomised, controlled, double-blind pragmatic clinical trial. AP patients aged 18–75 admitted within 72 h of onset will be assessed at admission for enrolment. We excluded the predicted mild acute pancreatitis (Harmless Acute Pancreatitis Score > 2 at admission) and severe organ failure (Sequential Organ Failure Assessment [SOFA] score of respiratory, cardiovascular, or renal systems > 3) at admission. Eligible patients will be randomly allocated on a 1:1 basis to CQCQD or placebo control administration based on conventional therapy. The administration of CQCQD and placebo is guided by the Acute Gastrointestinal Injury grade-based algorithm. The primary outcome measure will be the duration of respiratory failure (SOFA score of respiratory system ≥ 2) within 28 days after onset. Secondary outcome measures include occurrence of new-onset any organ failure (SOFA score of respiratory, cardiovascular, or renal system ≥ 2) and new-onset persistent organ failure (organ failure lasts > 48 h), dynamic surrogate biochemical markers and clinical severity scores, gut-centred treatment modalities, local complications status, intensive care need and duration, surgical interventions, mortality, and length of hospital stay. Follow-up will be scheduled on 6, 12, and 26 weeks after enrolment to assess AP recurrence, local complications, the requirement for surgical interventions, all-cause mortality, and patient-reported outcomes.

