## Introduction

### Background and rationale {6a}

Acute pancreatitis (AP) is an inflammatory disorder of the pancreas [1]. The common causes of AP such as gallstones, alcohol, hypertriglyceridaemia, endoscopic retrograde cholangiopancreatography (ERCP), and various drugs trigger self-digestion of acinar cells and induce local and systemic inflammation. It has an increasing prevalence with an overall incidence of over 34 affected cases per 100,000 person-years [2]. Most of the patients are uneventful and recover from mild disease (mild acute pancreatitis, MAP), or pull through local complications or transient organ failure defined as moderately severe acute pancreatitis (MSAP). Approximately 15–20% of patients manifesting persistent organ failure (POF) are defined as severe acute pancreatitis (SAP) [3], which are at risk of multiple organ failure (MOF) and the mortality can be up to 50% [4, 5]. Despite the global socioeconomic burden of disease, currently, there are no specific and effective therapeutic agents available to treat AP [6]. According to published guidelines [7, 8], supportive measures, such as analgesia, fluid therapy, nutritional supplementation, and organ support, remain the primary management modalities for AP patients.

Traditional Chinese medicine (TCM), which contains abundant multiple-target biologically active substances, has been broadly used in many countries and regions. Gastrointestinal dysmotility or dysfunction/failure, one of the common and complex complications in AP [9–11], is widely accepted as an important role in the pathogenesis of systemic inflammation and MOF [12–14]. Most TCM herbal formulas, such as dachengqi decoction [15, 16], qingyi decoction [17, 18], and rhubarb [19, 20], are used as an important “gut-centred” therapeutic strategy in the early treatment of AP [21]. Based on TCM theories, we summarised that the key pathogenesis of SAP-MOF is the invasion of “evil heat” to the organs, and its treatment requires “clearing heat, removing toxin, and purging the bowel” in clinical practice [22, 23]. Systematic reviews and meta-analyses of observational studies and trials with small sample sizes have demonstrated the effectiveness of rhubarb-contained TCM in reducing inflammatory markers, organ failure, local complications, and mortality, albeit the included clinical trials are of low quality [24–26].

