Chaiqin chengqi decoction (CQCQD) has been modified from dachengqi decoction and used to treat AP in our hospital for over 30 years [27, 28]. The comprehensive approach integrated by TCM and Western medicine improved clinical outcomes and reduced the mortality of SAP to 19.6% [29]. Our previous studies demonstrated that CQCQD can restore intestinal motility or ameliorate systemic inflammation via the toll-like receptor 4 and inflammasome-mediated pro-inflammatory pathways in AP models [23, 30].

Aiming to restoration or maintenance of gastrointestinal function, the Acute Gastrointestinal Injury (AGI) grade-based algorithm will be used to guide the administration of CQCQD [11]. Our trial protocol, informed consent, and other documents were submitted to the Biomedical Research Ethics Committee (BREC) of West China Hospital of Sichuan University in February 2020. After revisions, ethical approval was obtained on 22 June, 2020. The trial was registered with an identifier (ChiCTR2000034325) at chictr.org.cn on 2 July, 2020.

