## Statistical methods

### Statistical methods for primary and secondary outcomes {20a}

Data cleaning and statistical analysis will be performed by a statistician blinded to the whole trial process using the latest version of SAS software. The results of the data will be expressed as the means with ranges, medians with interquartile ranges, or numbers of patients with percentages. The comparison between the individualised CQCQD and control group is the primary interest in this study. Continuous variables are compared using the independent-sample *T* test or the Mann–Whitney *U* test (for non-normal distributions). Categorical variables are compared with the chi-squared test or Fisher’s exact test. Statistical tests will be two-sided, and *P* values < 0.05 will be considered significant.

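### Persistent organ failure is defined by duration alone, so a patient who dies within 48 h of onset with organ failure unresolved counts as having none

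*Protocol article*

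**What the plan says.** Under Secondary outcome measurements, the protocol article's first item covers new organ failure of any length and "new-onset of POF (organ failure lasts > 48 h". The Methods part of the abstract repeats the rule: "new-onset persistent organ failure (organ failure lasts > 48 h". The only qualifier concerns when the failure starts: "New onset is defined as events that occur after randomisation and not present 24 h before randomisation".

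The article treats POF as the mark of severe disease. Background and rationale {6a} says that "patients manifesting persistent organ failure (POF) are defined as severe acute pancreatitis (SAP".

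Death appears as a separate outcome within 26 weeks, "All-cause mortality", and is not joined to POF. Section {20a} gives the test for binary outcomes, "Categorical variables are compared with the chi-squared test or Fisher’s exact test", without a rule for patients who die. Section {20c} says "Missing values will be addressed by multiple imputation, having appropriately explored the missingness mechanism and in accordance with good practice" and does not mention deaths.

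**The concern.** A duration threshold works for patients who live long enough to pass or fail it. A patient who dies before 48 h with the organs still failing cannot pass it, so the definition places the worst course among the non-events. POF stands first in the secondary list, beside organ failure of any length, and is the article's own label for severe disease.

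The error has a direction. Each early death with unresolved organ failure takes one event away from its arm's POF count, so an excess of such deaths in one arm makes that arm look better on POF.

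**Working it through.** **Step 1: apply the definition to two records.**
- Record A: new respiratory and renal failure, resolved at 60 h. Duration 60 h > 48 h, so POF = yes.
- Record B: the same onset, no recovery, death at 30 h. Duration 30 h < 48 h, so POF = no.

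No other text changes record B. The new-onset rule is met in both records. Mortality is scored elsewhere. The imputation sentence does not reach record B either, because under the stated rule its status is known rather than missing.

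**Step 2: weight of one such patient.** The article gives no figure for POF, so there is none to reproduce. The arm size comes from Sample size {14}: 111 / 0.9 = 123.3, rounded up to 124 per group. With all 124 as the denominator, one patient is 1/124 = 0.8 percentage points.

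**Step 3: effect on the comparison.** Suppose the true risk of POF, counting early fatal organ failure, is equal in both arms. The spurious difference is (difference in early deaths) / 124:
- 2 v 2 early deaths: 0/124 = 0
- 4 v 2: 2/124 = 1.6 points
- 6 v 2: 4/124 = 3.2 points

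Each non-zero difference favours the arm with more early deaths. The death counts are illustrations, not forecasts.

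**Step 4: how many patients.** Inputs:
- 124 per arm, from Sample size {14}.
- 19.6% mortality in severe disease at this centre. Background and rationale {6a} says that combined treatment "improved clinical outcomes and reduced the mortality of SAP to 19.6" per cent. Since the article equates severe disease with POF, this rate belongs to POF patients.
- Assumed, with no source in the article: 30-40% of patients have new organ failure; 60% of that is truly persistent (counting early fatal cases); 10-30% of the deaths fall within 48 h of onset.

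Formula: misclassified per arm = 124 × (organ failure) × 0.6 × 0.196 × (early share).
- Low: 124 × 0.30 × 0.6 = 22.3 true POF; × 0.196 × 0.10 = 0.44
- High: 124 × 0.40 × 0.6 = 29.8 true POF; × 0.196 × 0.30 = 1.75

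As a share of true POF: 0.196 × 0.10 = 2% to 0.196 × 0.30 = 6%.

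**The case against.** The strongest reply is that the article is silent here rather than wrong. It never says how a death at 30 h is scored, and the analysis plan, which is not shown, could supply a rule. That could be so, and it limits how heavily the point should weigh. But the article does more than stay silent: it fixes an explicit threshold twice, and that threshold classifies the patient. An analysis plan that simply follows it would carry the result forward.

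Second, a reader might infer that early deaths disappear from the trial's results, or that preventing them earns no credit. The documents do not support that. The patient in record B is an event under organ failure of any length, which has no minimum duration, and under all-cause mortality. The outcome list joins any organ failure and POF with 'or'; if that were one composite, the patient would already be an event. The abstract joins them with 'and' and each has its own definition, so two outcomes is the more natural reading.

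Third, a reader might apply the 19.6% to all new organ failure. That gives 124 × 0.30 × 0.196 × 0.10 = 0.7 to 124 × 0.40 × 0.196 × 0.30 = 2.9 patients per arm, which overstates the problem because the figure is for severe disease only. The exclusion of any organ SOFA score above 3 at admission should lower early deaths further, though it cannot prevent later deterioration.

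Fourth, a reader might extend the point to the severe and nonsevere subgroups in {20b}. That section does not say how severity is derived, so the extension is not supported.

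**Conclusion.** The point holds as a small, directional flaw in one secondary outcome. As written, organ failure unresolved at death within 48 h of onset is scored as no POF, and each excess death of this kind improves that arm's POF rate by 0.8 percentage points at 124 per arm. The likely number is 0 to 2 patients per arm (0.4 to 1.75, or 2% to 6% of POF events). That range rests on the assumed organ-failure rate, persistent share and early-death share; the article gives no frequency of death within 48 h of onset.

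There is no between-arm bias if early deaths are balanced, and nothing in the article suggests an imbalance. The trial describes its framework as exploratory and POF is not the powered outcome, so this is an inexpensive correction and does not threaten the main result.

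**What to change.** In Secondary outcome measurements, define POF as organ failure lasting more than 48 h, or organ failure still present at death within 48 h of its onset. Report the strict count (more than 48 h only) alongside, so that readers can see how many patients the added clause moves. Make the change before unblinding and carry the same wording into the analysis plan; if the plan already has such a rule, only the wording needs aligning.

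The cost is one clause and one extra row in a table. The rule needs the time of organ-failure onset and the time of death; the study schedule is not shown, so the sponsor should confirm that the case report form records both. The downside is that POF will partly overlap with mortality and its count will be slightly higher. Treating death as a competing event is an alternative, but the added clause is simpler and fits the planned chi-squared or Fisher comparison.
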